#### Usual care: health management provided by the GP

The consult is intended to be as natural as possible so that the GP will not influence the quality of the usual care provided. Many GPs use the guidelines issued by the Dutch College of General Practitioners [14]. The guidelines for psychological complaints such as anxiety and depression describe management options as (anti-anxiety of anti-depressant) medication and/or 'watchful waiting' if a referral seems unnecessary [15].

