#### Health care utilization

The Trimbos/iMTA questionnaire for Costs associated with Psychiatric Illness (Tic-P) is used to measure the amount of health care received by the patients and to register sickness absence from work [29] Furthermore, we chose the EQ-5D (or Euroqol, [30]) because this is a standardized measurement instrument for a wide range of health conditions which provides a simple descriptive profile and a single index value for health status. The EQ-5D (or EuroQol) was originally designed to complement other instruments such as the SF-36, and it is administered to assess a patient's general health status, in 5 dimensions: mobility, self-care, usual activities, pain/discomfort and anxiety/depression[1]. Because each of the five dimensions can be sub-divided into 3 levels a total of 243 health states can be assessed. Using the Dolan model (1997) the total score will be expressed in utilities [31]. The official Dutch translation of the Euroqol will be administered [31,32]. Incremental cost-effectiveness ratios will be calculated, in which the difference in costs between intervention subjects and control subjects will be divided by the difference in effects between both groups. Incremental cost-utility ratios will also be calculated in which the difference in costs between the two groups will be divided by the difference in QALYs gained between the two groups.

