### Power/analysis

Randomization takes place at patient level. To evaluate the effects of the randomization, descriptive statistics will be used to compare the baseline measurements of the two groups. If necessary, differences between baseline variables on relevant characteristics (such as baseline HADS score) will be entered as covariates in the analysis.

To detect a clinically relevant difference between interventions (effect size of 0.4) with the primary outcome measure HADS (power of .90 and an alpha of .05) 130 completers are needed. In both conditions there will be 65 completers. We estimate the drop-out rate to be on 20%, so we therefore need 160 participants. If 20 practices cooperate, we will need to include 8 patients in every practice. We expect a non-response of 50%, so we will need to screen 16 patients in every practice. In a sample of patients with mixed symptoms of anxiety and depression, Cropper et al. [33]observed a mean overall HADS score of 6.25 at baseline. In the Dutch validation [16] the primary care patients have a mean on anxiety of 6.2 (SD 3.8) and 3.7(SD 3.4) for depression with a total mean of 9.9 (SD6.1). We consider a standardized mean difference (SMD) of 0.4 (p = 0,05) on the primary outcome (HADS) to represent a relevant improvement in the PST group versus the usual care group[34].

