#### Analysis

Linear regression models will be used to examine differences in investigate on the HADS. Scores will be entered in a repeated measure design (GLM), and (optional) covariates will be differences at baseline level. Repeated measures with several independent variables will be used to investigate differences in improvement in all secondary outcome measures between groups. The analyses will be performed on a per protocol basis ('completers'), as well as according to the 'intention-to-treat' principle. Trend analyses will also allow 'last observation carried forward' analyses. To assess whether protocol deviations have caused bias, the results of the intention-to-treat analyses will be compared with analyses of the PST group, including the completers.

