### Strengths and limitations

Many methodological requirements for a high quality trial are met [36]. Allocation is concealed through block-randomization by an external researcher. Recruitment of responders will be in the GP's waiting room, without the GP knowing where and how randomization will take place. The methodology used in this trial will overcome concerns of selection bias. The relevance to the Dutch primary care seems sufficient and the generalisability of our sample to patients in everyday practice seems high. The sample size is large, when compared to other trials on psychological problems in general practice [37]. Additionally, whether the outcome is negative or positive, the project will give a clearer understanding of who might or might not benefit from this treatment.

Another strength of this study is the chosen primary outcome, the self-report HADS. The HADS is a well-known questionnaire to measure reduction of symptoms of anxiety and depression. Many previous trials in psychiatry have relied on assessments of the therapist. Another strength is the combination of quantitative assessments and a qualitative process evaluation. If the psychiatric symptoms decline more in the intervention group than in the usual care group, we can therefore safely attribute this to PST treatment. If not, we will explore mechanisms This will provide useful information about implementing the intervention. A practical strength of the study is that the intervention can take place without disturbing care as usual, both in the study as in future implementation.

Some limitations of the present study need to be addressed. It is possible that patients are less motivated to attend PST treatment since screening of all participants takes place in the waiting room of the GP's. This may be lead to a higher dropout percentage in the PST-condition in comparison with the dropout percentage of the CAU.

This study may be criticized because of the lack of a control group without treatment. However, patients are always free to visit their general practitioners. Furthermore, naturalistic studies of the longitudinal course of anxiety and depression indicate that patients who have these symptoms longer than three months are suffering from chronic symptoms [38,39].

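### The stated check for bias from protocol deviations sets a between-arm effect against an analysis of the PST group alone, so it cannot show whether deviations biased the between-arm effect

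*Protocol article*

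**What the plan says.** The Analysis section of the protocol article plans repeated-measures models of the HADS and names two analysis sets: "The analyses will be performed on a per protocol basis ('completers'), as well as according to the 'intention-to-treat' principle". That sentence is not limited to one arm.

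The section then gives a separate diagnostic. Its purpose is "To assess whether protocol deviations have caused bias", and its method is that "the results of the intention-to-treat analyses will be compared with analyses of the PST group, including the completers". Usual care is not named in it.

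Two other places bear on the point. The Power/analysis section counts completers in each arm: "In both conditions there will be 65 completers". The Health care utilization section says the Tic-P "is used to measure the amount of health care received by the patients", again without restriction to one arm.

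**The concern.** An intention-to-treat result in a two-arm trial is a difference between arms. An analysis of the PST group is a result within one arm. It absorbs everything that changes HADS over time in those patients, including regression toward the mean after selection on a raised GHQ-12 and frequent attendance, as well as the effect of usual care, which the PST arm also receives. The two quantities would normally differ even if every patient followed the protocol. The check is also blind on one side, because non-completion under usual care cannot enter an analysis confined to the PST group.

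At stake is a statement in the eventual report that deviations did, or did not, bias the result. The Strengths and limitations section says that a larger decline under PST can safely be put down to PST. A reader would look to this check for part of the support, and as written it cannot give any.

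**Working it through.** The plan attaches no figure to this check, so there is none to reproduce. The check can be examined algebraically.

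**Notation.** Count improvement as a fall in HADS. Let P and U be the mean improvement of all patients randomised to PST and to usual care, and let Pc and Uc be the same means among completers.

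**Quantities named in the Analysis section**
- Intention-to-treat effect: P − U
- Analysis of the PST group, all patients: P
- Analysis of the PST group, completers: Pc
- Two-arm per-protocol effect: Pc − Uc

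**The check as worded**
- All PST patients: P − (P − U) = U
- PST completers: Pc − (P − U) = U + (Pc − P)

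The first gap is the usual-care improvement and says nothing about deviations. The second adds the effect of restricting to completers in the PST arm, but mixes it with U. The term Uc − U, the effect of the same restriction under usual care, appears in neither.

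**The like-for-like comparison**
- (Pc − Uc) − (P − U) = (Pc − P) − (Uc − U)

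Here U no longer appears as a separate nuisance term, and both arms enter symmetrically. This is the difference that shows how far restriction to completers moves the between-arm effect.

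**What agreement would mean.** The completer form of the check gives zero when U = −(Pc − P). That can happen with no selection and no usual-care improvement, or through cancellation. In either case Uc − U is unexamined, so agreement does not show absence of bias in the between-arm effect.

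**Illustration.** Inputs from the Power/analysis section are a standardized difference of 0.4 and a total-score SD of 6.1 from the Dutch validation sample. Applying that SD here is an assumption.
- P − U = 0.4 × 6.1 = 2.44 HADS points
- Assume U = 1 to 3 points; the article gives no value
- P = 2.44 + 1 = 3.44 to 2.44 + 3 = 5.44

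With no deviations at all, the two results would differ by 1 to 3 points. The range is only illustrative; the identity holds for any U.

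**What is left out.** The Design section allocates 80 patients per arm and the sample size allows for 65 completers per arm. By the plan's own figures that is 80 − 65 = 15 non-completers under usual care (15/80 = 18.75%). None of them can influence an analysis confined to the PST group.

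**The case against.** The strongest reply is that the sentence is loosely worded and not a real one-arm plan. It follows closely on a per-protocol analysis that is not limited to one arm, and completers are counted in both conditions. PST may be singled out only because non-completion of treatment arises there, and the Strengths and limitations section expects that dropout may be higher under PST. This is a fair reading, and it means the like-for-like contrast is already available in the plan. It does not rescue the sentence, which states a different comparison. If the sentence instead means PST completers against all usual-care patients, the gap from intention to treat is Pc − P, and usual-care non-completion is still ignored.

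A second reply is that U may be small, since the article argues that symptoms lasting beyond three months tend to be chronic. That would shrink the gap, but the check would still omit Uc − U.

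A reader might also infer three stronger criticisms, which the article does not support:

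- **That treatment obtained under usual care goes unexamined.** The Tic-P covers care received by the patients, and for the economic evaluation "the difference in costs between intervention subjects and control subjects will be divided by the difference in effects between both groups". No HADS analysis using these data is stated, but a condensed article may leave that to the full plan.
- **That such treatment is a deviation which dilutes the effect.** The guidelines cited for usual care "describe management options as (anti-anxiety of anti-depressant) medication and/or 'watchful waiting' if a referral seems unnecessary", and the PST arm receives usual care too. Such care is largely part of the comparator. The remark that "patients are always free to visit their general practitioners" answers criticism about the lack of an untreated control group and is not evidence of departures.
- **That a complier-average model is required.** With PST sessions as the treatment received, it carries no information on other care under usual care. With a yes/no measure of receipt and PST confined to one arm, it exceeds the intention-to-treat effect in size whenever attendance is incomplete. Comparing the two would not diagnose bias either.

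**Conclusion.** The point holds as a minor fault: the diagnostic is wrong as written. Followed literally, it compares quantities of different kinds. The gap equals mean usual-care improvement, plus a PST-only completer effect if completers are used, and it omits the corresponding term for usual care. That conclusion is algebraic and needs no assumed figure, except that P and U are taken to be means over all randomised patients. The 1 to 3 point illustration is assumed, and the article sets no threshold at which a difference would be called bias, so it should not be read as a predicted false signal.

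The intention-to-treat estimate of PST plus usual care against usual care alone is unaffected. So is the planned per-protocol analysis.

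**What to change.** Replace the sentence with wording such as: *To assess sensitivity to protocol deviations, the between-arm HADS estimate by intention to treat will be compared with the between-arm per-protocol (completer) estimate. Deviations and completion will be defined by one rule applied to both arms, and both models will use the same baseline adjustment, including baseline HADS. Care received, as recorded by the Tic-P, will be described by arm.*

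Drop the comparison with the PST group alone.

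The cost is a change of wording, a completion rule that makes sense in both arms, and one descriptive table from an instrument already in use. No new model is needed, because both estimates are already planned. The downside is that completers are self-selected and dropout may be higher under PST, so a gap between the two estimates could come from selection. It should be reported as sensitivity and not as proof of bias, and agreement should not be reported as proof that there was none.

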### Sample size

A GP in the Netherlands has an average of 80 consultations a week (children excluded). Six of the patients who consult their GP had done so more than three times in the previous six months and were 'frequent attenders'. With a response of 50%, three patients a week per general practice will be sufficient, but: only one third of them will meet the inclusion criteria. This implies that 1 patient can be included per practice per week. To include 160 patients with a screening in two practices per week, will take approximately one and a half years.

#### Arguments for publishing a design

The primary goal of presenting the design of this study before the results are available is to offer the reader the opportunity to consider the methodological quality of this study more critically and this is also a benefit for caregivers, because this extensive information provides more insight into the practical applications of the study intervention.

Publication also prevents publication-and-analysis bias. Trials that lead to adverse or negative results are less likely to be submitted for publication [35]. This can be avoided by publishing a priori the design of a study and the plans for analysis. Not only will the researchers be more inclined to publish the results, but transparency will also be increased and, in any case, data can be requested from the researcher for inclusion in a systematic review.

## Discussion

Our results may either confirm that PST in primary care is an effective way of dealing with emotional disorders and a promising addition to the primary care in the UK and USA, or may question this assumption. This trial will allow an evaluation of the effects of PST in practical circumstances and in a rather heterogeneous group of primary care patients.

### Strengths and limitations

Many methodological requirements for a high quality trial are met [36]. Allocation is concealed through block-randomization by an external researcher. Recruitment of responders will be in the GP's waiting room, without the GP knowing where and how randomization will take place. The methodology used in this trial will overcome concerns of selection bias. The relevance to the Dutch primary care seems sufficient and the generalisability of our sample to patients in everyday practice seems high. The sample size is large, when compared to other trials on psychological problems in general practice [37]. Additionally, whether the outcome is negative or positive, the project will give a clearer understanding of who might or might not benefit from this treatment.

Another strength of this study is the chosen primary outcome, the self-report HADS. The HADS is a well-known questionnaire to measure reduction of symptoms of anxiety and depression. Many previous trials in psychiatry have relied on assessments of the therapist. Another strength is the combination of quantitative assessments and a qualitative process evaluation. If the psychiatric symptoms decline more in the intervention group than in the usual care group, we can therefore safely attribute this to PST treatment. If not, we will explore mechanisms This will provide useful information about implementing the intervention. A practical strength of the study is that the intervention can take place without disturbing care as usual, both in the study as in future implementation.

Some limitations of the present study need to be addressed. It is possible that patients are less motivated to attend PST treatment since screening of all participants takes place in the waiting room of the GP's. This may be lead to a higher dropout percentage in the PST-condition in comparison with the dropout percentage of the CAU.

This study may be criticized because of the lack of a control group without treatment. However, patients are always free to visit their general practitioners. Furthermore, naturalistic studies of the longitudinal course of anxiety and depression indicate that patients who have these symptoms longer than three months are suffering from chronic symptoms [38,39].

Other potential criticism concerns the suitability of PST for primary care. Although PST seems suitable for primary care, provision of PST by trained nurses will not always be available in daily practice of small primary care practices.

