### PST provided by nurses as a potential option

Patients with psychological problems need more time than is available in general practice. The usual 10-minute consultation with a GP is generally too short to explain and explore these psychological problems. To complicate matters more, these problems are often interwoven with physical issues such as fatigue and sleeplessness. Furthermore, patients are ambiguous in presenting their symptoms [9]. Given this fact, in combination with the high prevalence of psychological problems in primary care, treating these patients will result in a shift of tasks to nurses. Especially nurses who are skilled in working with psychiatric patients, may become indispensable in primary care [10]. Nurses can be successfully trained in the techniques of PST and can provide effective PST for primary care patients [11]. Recent results show that a CBT protocol for panic-disorder can adhered by a therapist with minimal of or no CBT experience [12].

There are several issues which stimulate further investigation. First, PST may be the way forward in the Netherlands, where GPs have a heavy workload and patients need better tailored collaborative forms of care, focused on self-help and education.

There are still very few nurses working in Dutch general practice and although preliminary experiments are taking place to enhance and define the role of nurses in primary care, PST could be a welcome innovation in their task profile. So, innovative projects in primary care in the Netherlands are needed.

Secondly, there is a lack of research outcomes on the effectiveness of talking treatment for anxiety symptoms in patients. In this trial, patients with depressive as well as anxiety symptoms will be included. Only one study has reported substantially better outcomes for primary care patients with panic disorder, who received CBT and pharmacotherapy from a therapist with minimal or no CBT experience, like a nurse, than patients with usual care only from their GP [12].

Third, PST in primary care could prevent or stimulate a referral to secondary care for patients with complaints which cannot be treated in primary care. This would also stimulate better tailored collaborative forms of care and prevent the deterioration of complaints.

The primary aim of the present trial is therefore to investigate whether PST for patients with psychological problems provided by nurses in primary care, is effective.

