## Methods

### Design

A randomized, controlled trial is being carried out to evaluate the effects of PST. At least 160 primary care patients will be included; 80 will receive usual care and PST and 80 will receive usual care only. At baseline, after the intervention and after 3 and 9 months the patients will be asked to fill in a questionnaire, and at baseline and after 9 months they will be asked to cooperate in a (diagnostic) telephonic interview. Primary outcome is the reduction of symptoms, and other outcomes measured are improvement in problem solving skills, psychological and physical well being, daily functioning, social support, coping styles, problem evaluation and health care utilization.

The Medical Ethics Committee of the VU Medical Center in Amsterdam approved the study design.

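### The article predicts more dropout in the PST arm but plans for equal loss, does not separate stopping PST from leaving follow-up, and offers no measure against the imbalance

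*Protocol article*

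**What the plan says.** - **Expected imbalance.** Under Strengths and limitations, the article notes that waiting-room screening may yield patients with little motivation for PST, and continues: "This may be lead to a higher dropout percentage in the PST-condition in comparison with the dropout percentage of the CAU".
- **Planned loss.** Power/analysis makes one allowance without a split by arm: "We estimate the drop-out rate to be on 20%, so we therefore need 160 participants". It adds: "In both conditions there will be 65 completers". Design fixes the allocation: "80 will receive usual care and PST and 80 will receive usual care only".
- **Analysis sets.** Analysis plans a per-protocol analysis, glossed as completers, and an intention-to-treat analysis. The two are to be compared to see whether protocol deviations caused bias. Last observation carried forward is mentioned for trend analyses.
- **Follow-up.** Design plans questionnaires for the patients at baseline, after the intervention, and at 3 and 9 months, with no condition on attending PST. It also says that "at baseline and after 9 months they will be asked to cooperate in a (diagnostic) telephonic interview". The primary outcome, the HADS, is a 14-item self-report questionnaire.

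**The concern.** Two different events share one vocabulary. A patient can stop attending PST, or can stop returning questionnaires. Only the first is confined to the PST arm, because usual care has no course of sessions to leave. In Power/analysis a completer is a patient who counts towards the number needed for the HADS comparison. In Analysis a completer is a patient treated per protocol. Strengths and limitations then names poor motivation to attend as the expected cause of a higher dropout percentage.

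If the predicted imbalance takes the form of missing HADS scores, the PST patients left in the analysis are a selected group, with no matching selection by treatment motivation in usual care. A larger sample does not cure that. The article offers no measure against it, yet the same section says that a greater decline under PST could safely be credited to the treatment.

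**Working it through.** **1. The plan's own figures.** The dropout step reproduces closely: 130 / 0.80 = 162.5, so 163 against the stated 160. In reverse, 160 × 0.80 = 128, or 64 per arm against the stated 65. One rate is applied to both arms.

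The 130 itself does not follow from a plain two-group comparison at SMD 0.4, power 0.90 and alpha 0.05. Two-sided, 2 × (1.960 + 1.282)² / 0.4² gives 132 per arm, 264 in total. One-sided, 2 × (1.645 + 1.282)² / 0.4² gives 108 per arm, 216 in total. That is a separate matter and does not decide this point.

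**2. Does unequal loss cost power?** Inputs: 80 per arm and SMD 0.4 (stated); unadjusted two-sided test and split of loss by arm (assumed). Power = Φ(0.4 / √(1/a + 1/b) − 1.96), where a and b are the analysed PST and usual-care patients.

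| Loss PST / usual care | a / b | Power |
|---|---|---|
| 20% / 20% | 64 / 64 | 0.619 |
| 30% / 10% | 56 / 72 | 0.612 |
| 40% / 20% | 48 / 64 | 0.554 |

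With total loss held at 20%, shifting it towards PST barely matters. The third row is lower mainly because total loss is higher.

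**3. Does it cost bias?** Assume that PST patients with missing scores are 0.5 SD worse than PST patients with scores, and that usual-care loss is uninformative. With a fraction d missing in the PST arm, the observed contrast is too favourable by d × 0.5:
- d = 0.20: 0.10 SD
- d = 0.30: 0.15 SD, or 0.15 × 6.1 = 0.9 HADS points, using the SD of the Dutch validation sample quoted in the article
- d = 0.40: 0.20 SD

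If the same mechanism acts in both arms, only the difference counts: at 30% / 10% it is (0.30 − 0.10) × 0.5 = 0.10 SD, and at equal loss it is zero.

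**4. What would the named analyses show in the extreme case?** Assume that every patient who stops PST (share s) has no score after baseline, that PST adds 0.40 SD in attenders and nothing in stoppers, that everyone otherwise improves 0.5 SD, and that 10% of usual care is lost at random. The as-randomised effect is (1 − s) × 0.40. Completers show 0.40. Carrying baseline forward gives (1 − s) × 0.9 − 0.9 × 0.5.

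| s | As randomised | Completers | Carried forward |
|---|---|---|---|
| 0.20 | 0.32 | 0.40 | 0.27 |
| 0.25 | 0.30 | 0.40 | 0.225 |
| 0.30 | 0.28 | 0.40 | 0.18 |

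The two methods err in opposite directions. This is a boundary case: a stopper who returned the post-intervention or 3-month questionnaire would carry that score forward instead of baseline.

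**5. What does recovering scores achieve?** Take step 3 with d = 0.30 and recover half of the missing PST patients, assumed typical of those missing. The remaining bias is 0.15 − (0.15 × 0.5) / 0.85 = 0.15 − 0.088 = 0.062 SD. Recovering all of them removes it. In the 30% / 10% case, power rises from 0.612 to 0.657 (68 / 72) or 0.692 (80 / 72). The share recoverable is not known from the document.

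**The case against.** A reader might infer that non-attendance ends outcome data, and does so in the PST arm alone. The document does not support that. The limitation predicts that low motivation may raise dropout; it defines nothing. Questionnaires are planned for all patients, and an intention-to-treat analysis set beside the completers analysis suggests that data on non-completers are meant to be kept. The same sentence also speaks of a usual-care dropout percentage, so missing outcomes are not peculiar to PST.

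Nor can referral be brought in as a second route out of the study. The Background remark that "PST in primary care could prevent or stimulate a referral to secondary care" is rationale for the trial and says nothing about who stays in follow-up.

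It is also fair to say that definitions of dropout, follow-up of patients who stop treatment, and reminder procedures are commonly left to a full protocol, that the authors disclose the imbalance risk themselves, and that every bias figure rests on assumptions. The telephone call is no complete answer either: patients are asked to cooperate and may refuse, the interview is described as diagnostic, and the post-intervention and 3-month scores stay missing.

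All of this stands and limits the point. What it leaves is a mismatch inside the article, between equal planned loss and unequal expected loss, together with a double use of completers, and a planned contact that could reduce the loss at little cost.

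**Conclusion.** The point holds in a limited form, as a worthwhile and cheap improvement. The article predicts more dropout under PST, plans equal loss, does not separate stopping treatment from losing outcome data, and names no countermeasure. It contains no rule that ends follow-up when PST stops.

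The risk is bias, with little effect on power if total loss stays at 20%. Under the 0.5 SD assumption with uninformative usual-care loss, the bias is 0.10 to 0.20 SD for 20% to 40% PST loss, a quarter to a half of the 0.4 SD target. It is smaller if usual-care loss is informative in the same way, and absent if stoppers keep returning questionnaires. The document gives neither the split of loss by arm nor the outcomes of those lost, so these figures illustrate and do not predict.

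Full follow-up protects the intention-to-treat comparison. A per-protocol comparison remains selected whatever is collected.

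**What to change.** 1. State in Design that stopping PST is not withdrawal from follow-up, and that all randomised patients in both arms receive every questionnaire at the same times unless they withdraw consent to follow-up.
2. When the 9-month questionnaire is not returned, ask the 14 HADS items during the 9-month telephone interview already planned. Record the mode of administration and repeat the analysis without the telephone scores.
3. Report stopping of PST (PST arm) and loss of outcome data (both arms) as separate rates. Apply the 20% allowance to the second only, and use completers in one sense throughout.

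The cost is a few sentences and a few minutes in some calls. The drawback is that telephone answers may differ from paper answers, which the repeat analysis addresses. The gain is confined to the 9-month HADS of patients who agree to the call.
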